### At-Home Study Design

#### General Design

BioTechCOACH-ForALL home study is a prospective, multiple baseline across subjects, nonrandomized, single-arm, single-center study following a within-subject design to assess the feasibility and efficacy of the Virtual Coach Program in older age patients with HF. The study will be delivered in three phases, each of them fulfilling a different scope. All participants will go through all study phases. Each phase will allow participants to familiarize themselves with the delivered technology of that phase. A multiple baseline approach will be followed so that the effects of each phase are as isolated to the previous phases as possible, allowing for effect comparison among them. Clinical and quality of life assessment and exercise behavior and attitude will be measured repeatedly in both the baseline phase and the two intervention phases. This way any cause-effect relationships among the intervention and patient outcome measures will be demonstrated.

The study conforms to the ethical guidelines of the 1975 Declaration of Helsinki, all participants will sign informed consent, and the study protocol has been approved by the bioethics committee of the School of Medicine of the Aristotle University of Thessaloniki (Protocol No. 1.45/21.11.2018) and registered at ClinicalTrials.gov [NCT03877328]. The study protocol is structured in a manner that incorporates three different phases, coming one after the other. Each patient will enter the study in the phase 1 and complete their participation in phase 3.

#### Phase 1

Phase 1 introduces the objective measurement technology, the wearable monitoring device. This technology will be running throughout the project’s lifetime and will provide objective information on patient activity. This information, along with the doctor’s baseline and intermediate assessment, will be used as an indicator of the effectiveness of phases 2 and 3.

#### Phase 2

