Phase 2 introduces a joyful way of exercising, allowing patients to exercise in the comfort of their homes. Patients will be assigned a structured recommended schedule with a goal of 3 sessions per week for a total of 36 sessions in 3 months. Frequency and intensity of the training program are indicated by patient functional capacity. All patients will undergo a 6-minute walk test, and their performance will be used for determination of the exercise program. By protocol, patients performing more than 500 meters in the 6-minute walk test at baseline will be prescribed a more intense exercise program in terms of the number of exercise repetitions. The exercise protocol offers 50 minutes of exercise implementing aerobic and resistance endurance exercises including upper and lower extremities. Regular blood pressure and heart rate monitoring will be performed manually by the patient with the use of dedicated devices in time intervals specified in the protocol. Exercises will be implemented as fun, full-body interactions, processed and recognized through a depth-camera–based sensor and computer vision and translated into computer game actions and scenarios integrated within a Web application [14].

#### Phase 3

Phase 3 introduces the coaching aspects, where exergames are introduced and delivered through home surface projection, apart from the personalized recommendations and suggestions (designed by the doctor).

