### Clinical Assessment

Patients will be clinically evaluated before entering each of the two studies and on the initiation of each protocol phase (meaning before entering phase 1, phase 2, and phase 3, and at the end of phase 3, which will mark the end of study), completing 4 on-site clinical visits for the impact of each intervention to be assessed.

On the baseline, intermediate, and follow-up assessments, patient clinical condition, quality of life, and health-related costs will be considered. More specifically, blood pressure, heart rate, blood oxygen saturation, and body weight will be measured for the clinical assessment. To assess physical status, the 6-minute walk test and NYHA functional class will be used for exercise intolerance. Patient-related outcomes to be used include the Beck Depression Inventory [42] and the Dukes questionnaire [43]. As for the evaluation of quality of life, the Short Form Health Survey questionnaire [44,45] will be employed. Self-efficacy for exercise behavior scale will be used for evaluation of changes in patient perspectives on exercise [46]. Finally, for health-related costs, the effect on number of hospital admissions along with the effect on health care use (number of primary and secondary care contacts, social care contacts, relevant medication use) will be calculated during all three phases.

Real-world data will be collected continuously (across all phases of the home study) to assess several aspects of the interventions planned. Continuously measured activity levels expressed in daily steps taken by the patient will be compared across the different study phases. Real-life adherence of the HF patients to the proposed intervention will be measured in terms of attendance at the webFitForAll platform using wearable heart rate monitoring data as well as online activity logs and telephone and clinic follow-up. Real-world adherence will be compared within-subjects for the second and third phases of the study. Use analytics (virtual coach used, content and delivery time of messages/recommendations) of the e-coaching system and juxtaposed relevant outcomes (such as activity levels collected by the activity tracker and adherence to the webFitForAll training program given any system logs) will be routinely collected. Patients adherence will be evaluated by measuring attendance at the webFitForAll and heart rate monitoring data as well as by activity logs and telephone and clinic follow-up.

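### The home study is said to demonstrate cause and effect, but phase contrasts in a single-arm, fixed-order sequence with no specified onset stagger cannot be separated from time since entry, learning and carry-over

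*Protocol article*

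**What the plan says.** General Design (At-Home Study Design) calls the home study a "prospective, multiple baseline across subjects, nonrandomized, single-arm, single-center study following a within-subject design". It gives the purpose of that label: "A multiple baseline approach will be followed so that the effects of each phase are as isolated to the previous phases as possible". After noting that outcomes are measured repeatedly in the baseline phase and both intervention phases, it concludes: "This way any cause-effect relationships among the intervention and patient outcome measures will be demonstrated".

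The same section fixes the sequence. The protocol "incorporates three different phases, coming one after the other", and "Each patient will enter the study in the phase 1 and complete their participation in phase 3". It also expects patients to become familiar with each technology during its phase.

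On content, the Phase 3 paragraph says "Phase 3 introduces the coaching aspects, where exergames are introduced and delivered through home surface projection". The section on exergames places them in phases 2 and 3, and the e-Coaching section says that the last phase integrates all earlier components.

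On measurement and analysis, Clinical Assessment sets four visits at phase boundaries, continuous daily steps compared across phases, and this: "Real-world adherence will be compared within-subjects for the second and third phases of the study". Statistical Analysis names repeated measures ANOVA or the Friedman test between visits. Strengths and Limitations states that there is no distinct control group, that each case is its own control, and that analysis is on an individual basis.

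**The concern.** A multiple-baseline design across subjects supports causal inference when the intervention starts at different times in different subjects. If outcomes shift at each subject's own onset and not at a shared time, a time-driven explanation becomes unlikely. Repeated measurement and a fixed order do not supply this on their own.

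The comparisons at stake are steps across phases and adherence in phase 3 versus phase 2, on which a reader would judge whether exergames and e-coaching work. Without stagger or a control, each also carries time since entry, learning, change in novelty and, for phase 3, about three months of prior exergame training. A drift in either direction could be reported as a demonstrated effect, or could hide one.

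**Working it through.** **1. The requirement against the text.**
- Different onset times across patients: none specified. The article gives a duration for phase 2 (36 sessions in 3 months) but no length for phase 1. The Discussion uses the word staggered once, attached to the three-phase pilot, without saying that onset differs between patients.
- Control, washout or reversal: the study is single-arm and the phases are consecutive; neither washout nor reversal is described.
- Separation of phase 3 from phase 2: phase 3 keeps the exergames and adds projection, virtual coach and recommendations together.
- Analysis that uses onset or trend: the named tests compare visits, with no time term.

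**2. Can phase be separated from time since entry?** Take a model with patient effects, a free effect for each period since entry, and two phase-onset indicators. Illustrative assumptions: 9 patients, 12 periods.
- Columns: 9 + 11 + 2 = 22.
- Same onset times for all patients: rank 20. Each phase indicator is the sum of the period indicators from its onset on, so neither phase effect can be estimated.
- Three different sets of onset times across patients: rank 22. Both can be estimated.
- Same onset times, but time restricted to a straight line: 9 + 1 + 2 = 12 columns. These are independent, because a step is not a straight line. Phase effects then become estimable, but only because a trend form was assumed.

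Stagger would not settle phase 3 versus phase 2 entirely. Phase 3 always follows phase 2, so carry-over from training stays in that contrast.

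**3. The plan's own figure.** Inputs from Statistical Analysis: 3 time conditions (m), effect size f = 0.25, 80% power, 5% significance. Assumed, because not stated: correlation ρ = 0.5 and sphericity.
- λ = f²·n·m/(1−ρ) = 0.0625 × 28 × 3 / 0.5 = 10.5, with 2 and 54 degrees of freedom: power 0.812.
- At n = 27, λ = 10.125: power 0.796.

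So 28 is the smallest n reaching 80%, and the stated sample size is reproduced. (With ρ from 0 to 0.7, the required n runs from 53 to 17.) The sample size is not at issue here.

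**4. What the planned test does with drift alone.** Let the phase means be 0, d, 2d with no intervention effect. Their standard deviation is d·√(2/3) = 0.816d. Setting this to 0.25 gives d = 0.306 SD per phase. Rejection rates at the 5% level over 20,000 simulated trials (ρ = 0.5):

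| Assumed drift per phase | n = 9 | n = 28 |
|---|---|---|
| 0 | 4.9% | 4.7% |
| 0.1 SD | 7.5% | 13.9% |
| 0.2 SD | 15.0% | 43.9% |
| 0.306 SD | 30.0% | 81.0% |

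The n = 9 column reflects the statement that one-third of the 28 (28/3 = 9.3) go on to the home study. The last row matches the test's power for the planned effect (0.302 at n = 9, 0.812 at n = 28). The test responds to drift exactly as it would to an intervention effect of the same size.

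**The case against.** **Stagger may exist.** A reader might infer that onset is definitely the same for everyone. The article does not establish that. It is a condensed account, it names the design as multiple baseline across subjects, it uses the word staggered, and the Abstract has some participants through phase 2 while others are not. A fixed order is also compatible with a multiple-baseline design, since what varies there is onset time. This stands: the text supports only that no stagger across patients is specified. Rolling entry could help separate calendar time, but not time since entry, learning or carry-over.

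**The limitation is disclosed.** Strengths and Limitations admits the lack of a control group and mentions validity threats, and General Design claims isolation of phase effects only as far as possible. So it would be wrong to say that the authors overlooked the problem. But the mitigation offered is detailed reporting of context, and the causal sentence remains unqualified, so the two sections conflict.

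**The data are denser than four visits.** Daily steps and exergame attendance are logged continuously. This stands, and it makes a better analysis possible. The clinical and quality-of-life outcomes remain tied to the four visits.

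**The rejection rates are built in.** A test of equal means rejects when the simulation makes the means unequal; without drift its size is nominal. This also stands. Real drift might not be linear, and fading novelty could offset training gains.

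**Conclusion.** The point holds as a claim about what the described design can show. With one arm, a fixed order, no specified stagger, phase 3 layered on phase 2 and an analysis by visit without a time term, phase contrasts are confounded with time since entry, learning and carry-over. The unqualified cause-effect sentence is not supported and conflicts with the article's own limitation.

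The document gives no basis for the direction or size of any bias. A reader might take the 81% or 30% as the study's actual false-positive rate; they are consequences of an assumed linear drift and an assumed correlation of 0.5, and are not evidence that bias is present. The confounding itself does not depend on those assumptions. If the full protocol does specify staggered onset, the phase 2 contrast is better supported, but carry-over into phase 3 remains.

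**What to change.** **1. Replace the cause-effect sentence in General Design.** State that phase contrasts are uncontrolled within-patient before-after changes, and that phase 3 versus phase 2 evaluates the whole e-coaching package added after prior exergame training. This brings the section into line with Strengths and Limitations. Cost: wording.

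**2. Add a trend-aware analysis of daily steps.** Fit a within-patient interrupted time series with phase and time in study, and read a phase effect only as a change of level or slope beyond trend. State the assumed trend form in advance. Treat the result as supportive: one-third of 28 is about 9, Results reports 10 patients included, and step 2 of the working shows that the estimate rests on the trend form if onset is common. Cost: analysis only, on data already being collected.

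**3. State whether phase 2 onset differed across patients.** If it did, say how it was set and use the actual onset times in the model. Cost: one sentence and existing dates.

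**Optional.** Randomly assigned baseline lengths could be used for any patients not yet in phase 2, at the cost of an amendment and longer baseline wear for some. This may come too late: Results says that recruitment is completed and the project has progressed through phase 2, although the Abstract says recruitment is ongoing. It would not remove carry-over from phase 2 to phase 3.

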### Patient Population

Both studies can fulfill their objectives only if appropriate subjects are enrolled. The following eligibility criteria are designed to select subjects. These criteria must be met before a subject is assigned to the study. Subject eligibility should be reviewed and documented by a qualified member of the investigators’ study team before subjects are included in the study. All patients included in the study protocol will undergo all three home study phases, in addition to the EEG experiment in the lab. For the latter phase, a percentage of patients, without the need to proceed with the whole study protocol, will be recruited.

### Selection Criteria

Subjects must meet all of the inclusion criteria to be eligible for the enrollment:

Male and female patients aged over 55 years with HF of any etiology, with either reduced or preserved ejection fraction, diagnosed according to international guidelines [7]Must be in New York Heart Association (NYHA) functional class II-IVMust be in stable clinical condition and on stable medical treatment for the underlying disease for at least 3 months prior to inclusion to the studyMust be willing and able to comply with scheduled visits, treatment plan, and trial proceduresMust provide personally signed and dated informed consent document indicating that the subject has been informed of all pertinent aspects of the study

Subjects presenting with any of the following will be excluded from the study:

Unstable disease with evidence of decompensation, recent hospitalization, or undergoing investigation for clinical deteriorationRecent history of chest pain, palpitations, light-headedness, dizziness, or syncope on exertionContraindications to physical activity or with physical obstruction to perform the prescribed training program (eg, patient uses wheelchair)Any severe acute or chronic medical or psychiatric condition that may increase the risk associated with trial participation or interfere with interpretation of trial resultsInvestigational site staff members directly involved in the conduct of the trial and their family members; site staff members otherwise supervised by the investigatorParticipating in any other experimental studiesNot willing to provide signed informed consent

### Materials and Technologies

The technologies to be used for BioTechCOACH-ForALL along with their scope are presented in Figure 1 and include wearable continuous monitoring and lifestyle patterns discovery, exergames, and projected, smart e-coaching.

**Figure 1 figure1:**
[figure not shown]
Protocol phases and technology introduced in each phase.

#### Wearable Monitoring

The wristband monitoring device (Wavelet Health) [34] includes a clinical-grade (red plus infrared) photoplethysmogram sensor along with accelerometer and gyroscope and can collect continuous physiological and activity data processed using robust algorithms. Actigraphy capture rates spanning from 1 Hz to 20 Hz, while light sensor capture rate can be either 43 Hz or 86 Hz. To balance energy consumption, light sensor capturing is enabled in cycles. This means it does not measure all the time, but it remains idle for some time and collects a single averaged measurement over the remaining time of the cycle.

Computed features include steps, calories, beats per minute, heart rate variability, SpO_2_, breathing rate, sleep staging (awake, light, deep), and total sleep time. These fitness and lifestyle analytics will be calculated both as intraday and interday time series so as to form different patterns within a day (allowing the system to understand daily habits) and trends in specific time periods (to quantify health and lifestyle changes). Different detailed levels of information will be explored like per minute or hour. Active time periods against sedentary moments will also be used as a way to explore patients’ activity habits during the day.

Collected information will be used as objective, real-life measurements for evaluation of different interventions compared with the baseline (activity levels as proxy indicator for active lifestyle habits) and as a way to personalize different parameters of the intervention (eg, time of the day or weekdays to suggest that patients perform exercise regimes).

#### Exergames Promoting Physical Exercise

In order to deliver a structured protocol of physical exercise to HF patients, a computerized intervention will be developed in the form of exergames as part of home study phases 2 and 3.

An existing exergame platform, webFitForAll [14], incorporates physical exercises recommended by the American College of Sports Medicine and American Heart Association [29] focusing on upper and lower strength, stretching and flexibility, and aerobic exercise, will be used for delivery of the tailor-made physical exercise program. An example of the webFitForAll interface is presented in Figure 2.

**Figure 2 figure2:**
[figure not shown]
webFitForAll interface.

Adherence to the right execution of exercise is feasible by comparing several predefined parameters concerning the movements of patients. Joint angles are continuously monitored based on the tracking of body skeleton joints having as inputs the MentorAge device (Nively SAS) embedded RGB and infrared cameras, thus providing smart feedback to patients with respect to successful execution of the exercises. This mechanism ensures correct administration of the protocol and adherence of the patient to the instructions. webFitForAll allows patients to track their progress by evaluating their in-game performance with a single score. Motivational messages are delivered at the end of a game and the end of a training session to keep patients engaged with the intervention.

#### e-Coaching

This is the most important part of the solution (introduced at the last phase of the home study) since it integrates all previous components and their respective information while being the main patient-system interaction point. Daily recommendations about activity and patient self-management together with a virtual coach that will be selected based on findings of the neurophysiological study will be projected on a predefined surface in the patient’s home. The type of messages and time of delivery will be chosen/scheduled based on the personal profile of the patient (eg, nocturnal patterns of activity). Leaving the home environment intact is considered key to increase the acceptance of the e-coaching system by the patient. Therefore, any information visualization will happen only at predefined moments and will disappear instantly, by simply turning the projector off.

An added value of the study is personalization of the e-coaching system by means of evaluating the virtual agent characteristics using EEG, eye gaze tracking, and other physiological measurements.

### Procedures

Apart from the home study, a study in laboratory settings will be conducted to explore the design elements of the virtual agent that will be part of the e-coaching technology. Participants will undergo a 2-part experimental procedure in order to investigate the impact of different appearance-related characteristics of virtual coaches on user engagement, set up as follows: the study takes place in a magnetically shielded, sound attenuated, and dimly illuminated room hosted in the Laboratory of Medical Physics. EEG recordings are performed by means of a 128-channel EEG recording system (Nihon Kohden Corp) and a sponge-based passive electrode system (R-Net cap, Brain Products GmbH) applying the international 10-20 positioning system. Participants are comfortably seated in an armchair in front of a 23.5-inch computer monitor at a distance of 75 cm.

In the first part, the HF patients initially undergo EEG recordings during resting state with eyes closed (5 minutes). Participants then passively view 32 agents presented on screen as stimuli in a random order, grouped with respect to their appearance characteristics such as age, gender, and presence/absence of medical uniform (Figure 3A). During each trial, the stimulus (image of a virtual agent, height 6.22 cm, width 4.57 cm) is presented for 2000 ms in the center of the screen followed by a 2000 ms interstimuli period during which a black screen with a fixation cross is displayed. Each participant completes 256 trials (128 trials displaying images of virtual agents, 128 trials displaying black screen with fixation cross). In the second part, the stimuli presented to the participants during each trial consist of pairs of virtual agents and a fixation cross between them. The pair of agents differ regarding the presence/absence of medical uniform but are similar with regard to all other characteristics (age, gender; Figure 3B). Each stimulus appears for a duration of 2000 ms followed by an interstimuli period of 2000 ms, during which a black screen with a fixation cross is displayed in the center of the screen. The overall number of trials in this second part is 512 (256 trials displaying pairs of virtual agents, 256 trials displaying black screen with fixation cross) [35]. In both parts, participants are instructed to freely observe the images of virtual agents. During the EEG study, electrodermal activity, blood volume pulse, external body temperature, and eye gaze tracking are recorded for each participant. Biosignals will be collected by means of an E4 smartwatch (Empatica Inc), while eye gaze tracking will be performed using a GP3 eye tracker (Gazepoint).

